### Outcomes

Evaluations of complex interventions usually require a complementary use of quantitative and qualitative methods, to investigate and inform the process [41]. Following Proctor et al.’s framework for implementation research outcomes, our study comprises implementation outcomes (acceptability, adoption, appropriateness, fidelity, penetration, and costs), service outcomes (efficiency, effectiveness, and patient-centeredness) and client outcomes (satisfaction, function, and symptomatology) [42].

### Intervention fidelity

In this part, we seek to quantify the implementation of the selected national guidelines by employing three five-point fidelity scales, where 1 equals poor fidelity and 5 equals high fidelity. Researchers use such scales to assess and influence the implementation process based on the hypothesis that the replication of core elements, previously tested through rigorous research designs, will achieve similar outcomes [43, 44]. We use one scale to assess the practice and content of family psychoeducation (scale 1) and a general organisational index (GOI) scale (scale 2) to assess the organisation, penetration rate, and general integration of family psychoeducation in the unit’s clinical practice. These scales were used in BPB and demonstrated robust psychometric properties [45, 46]. The third scale (scale 3) gives a composite assessment of structure, content, implementation, and penetration rate of basic family involvement and support. The project group developed the latter scale to measure other elements of the IFIP intervention. Thus, our fidelity instruments measure both fidelity and penetration rate, as defined by Proctor et al. [42].

#### Data collection

Project members will measure fidelity on site visits, by the aid of interviews with clinicians, leaders and resource-persons, as well as written material, observations, and quantitative data (e.g. the number of eligible patients who receive family psychoeducation). Each assessment team will consist of two persons to counteract bias and be able to calculate inter-rater reliability. The raters will score fidelity independently and then sort out any discrepancies to reach a consensus score. Clusters in the intervention arm will be scored at baseline, and with new assessments at 6, 12, and 18 months after the implementation start date, whereas units in the control arm will be measured at baseline and 18 months only. This is both to allocate our resources effectively and to avoid influencing the control clusters through repeated fidelity measurements.

#### Outcomes and data analysis

Project members scored baseline fidelity before randomisation of the clusters, to counteract experimenter bias. To complete objective three, we will examine the baseline fidelity scores and analyse their distribution in both arms, while exploring contributing factors such as cluster characteristics. We will investigate the psychometric properties of all three fidelity scales. When addressing objective two, we will compare change in fidelity to the intervention after 18 months, between the two arms, controlling for baseline fidelity and other relevant covariates. These latter changes constitute the IFIP trial’s only primary outcomes. These outcomes will be reported as change in total fidelity, change in fidelity scales 1, 2, and 3 separately, and for scale 3; change in the subscale for penetration rate and change in the subscale for content, structure and implementation, respectively. The two additional fidelity measurements in the intervention arm will help us monitor and influence the implementation process closely. We will employ analysis of variance (ANOVA) models for the statistical analysis.

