**Methods:**

The trial is cluster randomised, where 14 outpatient clusters from community mental health centres undergo stratified randomisation with an allocation ratio of 1:1. The seven intervention clusters will receive implementation support for 18 months, whereas the control clusters will receive the same support after this implementation period. The intervention consists of: 1. A basic level of family involvement and support. 2. Family psychoeducation in single-family groups. 3. Training and guidance of health care personnel. 4. A family coordinator and 5. Other implementation measures. Fidelity to the intervention will be measured four times in the intervention arm and two times in the control arm, and the differences in fidelity changes between the arms constitute the primary outcomes. In each arm, we aim to include 161 patients with psychotic disorders and their closest relative to fill in questionnaires at inclusion, 6 months and 12 months, measuring psychosocial health and satisfaction with services. Clinicians will contribute clinical data about patients at inclusion and 12 months. Use of health and welfare services and work participation, for both patients and relatives, will be retrieved from national registries. We will also perform qualitative interviews with patients, relatives, health care personnel and leaders. Finally, we will conduct a cost-effectiveness analysis and a political economy analysis.

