### Selection, sample size and allocation of clusters

To be eligible as clusters, clinical outpatient units had to be part of a participating CMHC and have the main responsibility of treating patients with psychotic disorders in their discrete geographical catchment area. We accepted all types of clinical outpatient units, from Flexible Assertive Community Treatment teams (FACT) [34] to stationary outpatient clinics. The study recruited both clinics solely dedicated to the treatment of psychotic disorders and units covering a wider spectrum of conditions, including substance abuse and bipolar disorder. Some of the centres had multiple outpatient units caring for patients with psychotic disorders. When these covered the same area, we invited all of them to participate in the same cluster. After having recruited 15 clinical units in total, the project had to join two of them in order to have 14 clusters for randomisation. We merged the two units who collaborated the most into a single cluster, and these came from different CMHCs. In line with the pragmatic nature of the trial, there were no exclusion criteria for clusters.

Based on the average results from the NEBP project [31] and similar research we used a mean difference in fidelity scores of 1.82 with an average standard deviation (SD) of 0.80, after 18 months of implementation support to calculate sample size [35, 36]. Choosing 5% two-tailed significance and 80% power, we estimated that 4 clusters in each arm were needed to show that implementation support gives a significant increase in fidelity, compared to baseline or low fidelity. Since these previous studies were not randomised, a premise for this calculation is that the mean fidelity will not change in the control arm. To secure sufficient power in the quantitative study on patients and relatives (see below), we recruited 7 clusters to each arm.

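### Six overlapping fidelity changes share primary status for one primary objective, and the sample size is tied to none of them; if any one significant result counts as success, the false-positive chance is about 10–23% rather than 5%.

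*Protocol article*

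**What the plan says.** The Primary objective section of the protocol article asks one question: whether the implementation support goes with a higher level of implementation of the selected guideline recommendations.

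Under Intervention fidelity, Outcomes and data analysis, the between-arm comparison of fidelity change at 18 months is given this status: "These latter changes constitute the IFIP trial’s only primary outcomes". The next sentence lists the measures: "These outcomes will be reported as change in total fidelity, change in fidelity scales 1, 2, and 3 separately", and then, for scale 3, "change in the subscale for penetration rate and change in the subscale for content, structure and implementation, respectively". That is six measures: total, scale 1, scale 2, scale 3, and two parts of scale 3. The Methods paragraph of the abstract also uses the plural: "the differences in fidelity changes between the arms constitute the primary outcomes".

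The section on selection, sample size and allocation of clusters works with one fidelity score: "we used a mean difference in fidelity scores of 1.82 with an average standard deviation (SD) of 0.80". It continues: "Choosing 5% two-tailed significance and 80% power, we estimated that 4 clusters in each arm were needed". It does not say which score this is. For the sake of the patient and relative outcomes, "we recruited 7 clusters to each arm".

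**The concern.** One objective needs one answer. As written, six measures can each be called a primary result, and nothing in the article says which one decides or how a split result would be read.

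A split result is realistic. Scales 1 and 2 concern family psychoeducation, while scale 3 concerns basic family involvement and support. Scale 3 was developed by the project group, and the article reports earlier psychometric results only for scales 1 and 2. Fidelity is scored by project members, and the Blinding section says that the project's researchers are not blinded. A difference confined to one subscale of scale 3 could therefore be presented as a primary finding of the trial.

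The 5% level used for the sample size belongs to one test. It is the error level of the primary claim only if one test decides that claim.

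**Working it through.** **1. The plan's own figure.** Inputs from the cluster sample-size section: difference 1.82, SD 0.80, two-sided 5%, power 80%.

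n per arm = 2 × (1.960 + 0.842)² × (0.80 / 1.82)² = 3.03, rounded up to 4. This matches the stated 4 clusters per arm, and it is a calculation for one comparison at 5%.

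**2. Six tests if they were independent.** 1 − 0.95⁶ = 0.265. This is only an outer bound. The six cannot be independent, because scale 3 overlaps with its own subscales and the total overlaps with the scales.

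**3. Six tests with the overlap modelled.** Simulation with no true difference on any measure, 7 against 7 clusters, and two-sided t-tests at 5% on 12 degrees of freedom. There are four components: scale 1, scale 2 and the two scale-3 subscales, with a common correlation r. Scale 3 is taken as the mean of its two subscales, and the total as the mean of the three scales. These weights and the values of r are assumptions. The result is the chance that at least one of the six tests is significant:

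| Assumed r | At least one of six significant |
|---|---|
| 0 | 22–23% |
| 0.3 | 19–20% |
| 0.5 | 17% |
| 0.7 | 14% |
| 0.8 | 12% |
| 0.9 | 10% |
| 0.95 | 8% |

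Where a range is shown, repeated runs differed in the last digit. The total alone was significant in 5% of runs at every r, as it should be. Unequal weights changed little: with weights of 0.5, 0.2 and 0.3 for the scales and 0.4 and 0.6 for the subscales, the result was 22% at r = 0 and 17% at r = 0.5.

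**4. Power with 7 clusters per arm, SD 0.80** (noncentral t):

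| True difference | One test at 5% | Bonferroni, 0.05 / 6 = 0.0083 |
|---|---|---|
| 1.82 (plan) | 97% | 84% |
| 1.5 (assumed) | 90% | 64% |
| 1.3 (assumed) | 80% | 49% |

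A single named primary outcome keeps the middle column. Splitting the 5% over six tests is affordable only at the full planned difference.

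**The case against.** The strongest reply is that the article describes one construct, fidelity at 18 months, shown first as a total and then broken down. The list opens with the total, and the verb is about reporting, not testing. On that reading nobody intends to claim success on any one of six, and the inflation does not arise. Nor would it arise if all six had to be significant. This stands in part: the article states no success rule, so the percentages above are conditional on the any-of-six rule. It does not remove the point. The text speaks of primary outcomes in the plural, in the abstract as well, and being first in a list is not the same as being named decisive.

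A second reply is that testing order and multiplicity adjustment may properly sit in the statistical analysis plan or the full protocol, neither of which is shown. That is right, and a reader should not infer that the trial has no error control. The point rests on what this article itself fixes, which is equal primary status for six measures.

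A third reply is technical. The article plans ANOVA models controlling for baseline fidelity and other covariates, not plain t-tests, and gives neither weights nor correlations. The simulation therefore shows the order of size and is not an estimate for this trial.

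A reader might also infer that adjusting over all six would cost little, because power stays at 84%. That holds only at the full difference of 1.82. This figure comes from non-randomised studies and presumes no change in control-arm fidelity, whereas the Discussion expects new clinical pathways to affect both arms.

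**Conclusion.** The point holds in this form: the article gives six overlapping fidelity changes equal primary status for one primary objective, and it sizes the clusters on one unspecified fidelity score at two-sided 5%. If a significant result on any one of the six counts as success, the chance of a false positive primary result is about 10–23% for correlations from 0.9 down to 0, and about 14–19% for correlations from 0.7 down to 0.3. It can fall below 10% if the measures are almost collinear (8% at 0.95), but it stayed above 5% at every correlation tried. These figures rest on the any-of-six rule, equal weights and assumed correlations.

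A reader might infer 26% from six tests at 5%. The article does not support that figure, because the measures overlap and it would require independence.

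This should be fixed before the 18-month comparison. It calls for a clearer definition of the primary outcome and does not show that the design is unsound.

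**What to change.** Name change in total fidelity at 18 months as the single primary outcome, tested at two-sided 5%, and state how the total is formed from the three scales. Say in the sample-size section that the assumed 1.82 and SD 0.80 refer to that total, or justify them for it. Make scales 1, 2 and 3 key secondary outcomes, tested by Holm only if the total is significant. Report the two scale-3 subscales descriptively, with confidence intervals. Use the same wording in the abstract, the analysis plan and the registry entry.

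The cost is wording only: no further clusters or data, and no loss of power on the primary test. The downside is that a success on one scale without a difference in the total can no longer be called a primary result.

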### Patients’ and relatives’ quantitative outcomes

The main purpose of this part is to determine whether a higher level of implementation of family involvement is associated with relevant and favorable outcomes for patients and relatives, as put forth in objective six.

#### Sample size

All the outcomes of this part are secondary outcomes. With regards to sample size however, for patients we elected the ‘interpersonal relationships’-subscale from the Behavior and Symptom Identification Scale (Basis-24) (questions 4–8). This instrument covers six domains: depression/ functioning, interpersonal relationships, self-harm, emotional lability, psychosis, and substance abuse, as seen from the patient’s perspective, and has shown good reliability and validity [47]. For relatives we chose the outcome ‘experienced support’ measured with the Carer Well-being and Support (CWS) questionnaire short version 2 part B. This part measures support from the health services, as experienced by the relative, with demonstrated good reliability. However, validity for this scale was not available, due to the lack of appropriate validating measures [48]. Since we have not found comparable studies that have published data on these instruments, we decided to use a 0.5 SD improvement (medium effect) when calculating the sample size. With 80% power and 5% two-tailed significance, we would need 64 patients and 64 relatives in each arm, in a study with individual randomisation. For our cluster randomised trial, assuming an intraclass correlation coefficient (ICC) of 0.05 and having 7 clusters in each arm, we need 112 patients and 112 relatives in each arm. Calculation is done as defined for cluster randomised trials in health services research [49, 50] and the elaboration of the CONSORT statement in relation to cluster randomised trials [51, 52]. Taking into account the possibility of a 30% drop out, we need to recruit 161 patients and 161 relatives per arm.

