The project group generated a sequence by ranking the clusters from 1 to 14, according to their current number of patients with psychotic disorders. We then stratified the clusters into three blocks; 4 clusters with between 130 and 217 patients, 6 clusters with between 60 and 129 patients, and 4 clusters with between 1 and 59 patients. Within each block, the clusters were randomised to either the intervention or the control arm, with an allocation ratio of 1:1. An independent statistician performed the allocation, drawing 14 numbers using the Microsoft Excel RAND-function, being blind to both the sequence of clinical units and the stratifying variable. The purpose of doing stratified randomisation was primarily to achieve a balance in the number of patients and relatives between the two arms, and secondly to include units of various sizes in both. Since the larger units are located in metropolitan areas, the stratification inadvertently resulted in both urban and rural clusters in each arm.

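### The 80% power stated for 112 patients or relatives per arm rests on individual-trial degrees of freedom and equal clusters; with 14 clusters an unadjusted comparison has about 74%, or about 70% if recruitment follows caseload

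*Protocol article*

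**What the plan says.** All figures are in the protocol article. Under Patients' and relatives' quantitative outcomes, Sample size, the effect is set by convention because no comparable published data were found: "we decided to use a 0.5 SD improvement (medium effect) when calculating the sample size". The individual-randomisation step follows: "With 80% power and 5% two-tailed significance, we would need 64 patients and 64 relatives in each arm". The cluster step is "assuming an intraclass correlation coefficient (ICC) of 0.05" and "having 7 clusters in each arm, we need 112 patients and 112 relatives in each arm". The last step is "Taking into account the possibility of a 30% drop out, we need to recruit 161 patients and 161 relatives per arm". The same section says that every outcome in this part is secondary.

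Under Selection, sample size and allocation of clusters, this calculation is the reason given for the number of clusters: "To secure sufficient power in the quantitative study on patients and relatives (see below), we recruited 7 clusters to each arm". The fidelity outcome needed only 4 per arm. That section also gives three size blocks: 4 clusters with 130 to 217 patients, 6 with 60 to 129, and "4 clusters with between 1 and 59 patients". On allocation it says: "Within each block, the clusters were randomised to either the intervention or the control arm, with an allocation ratio of 1:1".

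Under Recruitment, all eligible patients are to be approached, and no quota per unit is stated. Under Data analysis, the model is a generalised linear mixed model with the treatment unit as a random effect.

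**The concern.** The design effect corrects the variance for clustering. It does not correct the reference distribution. Arm is a cluster-level factor, so its effect is judged against variation between 14 clusters, and the critical value is about 2.18 rather than 1.96. At this number of clusters, that difference costs several points of power. The design effect used also holds for a common cluster size, whereas the blocks show large differences in caseload.

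The number of clusters and the target of 161 per arm both rest on this calculation. If true power is nearer 70-74%, the chance of missing a real 0.5 SD effect on interpersonal relationships or experienced support is about 26-30%, not 20%. A null result on those outcomes would then be weaker evidence than the stated 80% suggests.

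**Working it through.** **Inputs from the protocol article:** effect 0.5 SD; two-sided 5%; 80% power; ICC 0.05; 7 clusters per arm; 112 analysed per arm; 30% dropout; the three caseload blocks.

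**1. Reproducing the stated figures**
- Individual randomisation, two-sample t-test: 63.8, so 64 per arm.
- Size per cluster with 7 clusters fixed: m = n(1 − ICC)/(k − n × ICC) = 64 × 0.95/(7 − 3.2) = 60.8/3.8 = 16.
- Per arm: 7 × 16 = 112. Check: design effect 1 + 15 × 0.05 = 1.75, and 64 × 1.75 = 112.
- Dropout: 16/0.7 = 22.9, so 23 per cluster, and 23 × 7 = 161.

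All three figures are correct for the method used.

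**2. Power of 112 per arm, equal clusters**
- Effective number per arm: 112/1.75 = 64.
- Noncentrality: 0.5 × √(64/2) = 2.83.

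| Reference distribution | Power |
|---|---|
| Normal | 80.7% |
| t, 126 df (2 × 64 − 2) | 80.1% |
| t, 12 df (14 − 2) | 73.8% |
| t, 10 df (three blocks fitted) | 72.2% |

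The stated 80% therefore needs individual-trial or large-sample degrees of freedom. Simulating cluster means (40,000 replicates) gave 73.9% power on 12 df with type I error of about 5%. Testing the same statistic against 1.96 restored about 80% power, but raised type I error to 7.2-7.5%. In a separate mixed-model simulation, Wald z-tests had type I error of 6.2% with equal clusters and 7.3% with unequal clusters.

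**3. Unequal clusters**

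This step assumes recruitment proportional to caseload, with each cluster at its block midpoint (173.5, 94.5 and 30) and 2, 3 and 2 such clusters per arm.
- Total caseload per arm: 2 × 173.5 + 3 × 94.5 + 2 × 30 = 690.5.
- Scaled to 112 analysed: about 28.1 (two clusters), 15.3 (three) and 4.9 (two); coefficient of variation 0.55.
- Effective number, Σ m/(1 + (m − 1) × 0.05): 2 × 11.94 + 3 × 8.93 + 2 × 4.08 = 58.8.
- Noncentrality: 0.5 × √(58.8/2) = 2.71. Power is 70.2% on 12 df and 68.6% on 10 df.

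Drawing caseloads at random within the blocks gives a median of 69.6% on 12 df (95% of draws 67.5-71.2%). These figures assume efficient weighting of clusters.

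**4. Difference detectable with 80% power on 12 df**
- The noncentrality needed is 3.05.
- Equal clusters: 3.05/√(64/2) = 0.54 SD.
- Proportional recruitment: 3.05/√(58.8/2) = 0.56 SD.

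**5. What baseline adjustment could do**

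The document gives no baseline correlation r, so this is a range under assumption. The first three columns suppose that adjustment removes a share r² of all variance.

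| r | Equal clusters | Proportional | If only within-cluster variance falls |
|---|---|---|---|
| 0.3 | 77.7% | 74.2% | not computed |
| 0.5 | 85.0% | 82.0% | about 76-80% |

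**The case against.** The strongest reply is that nothing is miscalculated. The values 64, 112 and 161 all reproduce, and the method is a standard design-effect inflation with named sources. That is right: the arithmetic is correct. What does not follow is the power attached to it.

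Several stronger readings are tempting, and the document does not support them.

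- *The calculation overlooks that there are few clusters.* It does not. The 7 per arm determine the 16 per cluster. Only the degrees of freedom and the variation in size are left out.
- *No valid test has more than 70-74% power.* Those figures are for an unadjusted comparison at one time point. The scores are collected at inclusion, 6 and 12 months, and the choice of baseline adjustment and degrees-of-freedom method may properly sit in an analysis plan that is not shown. Step 5 shows that adjustment could bring power back to 80% or more. But the sample size section takes no credit for it and gives no correlation, so it cannot support the 80% as stated.
- *The design has 70% power.* That value depends on proportional recruitment at block midpoints. The blocks and the rule of approaching all eligible patients make unequal numbers likely, but consent, the exclusion criteria and the payment to units per recruited pair could change the pattern. The 74% needs no such assumption.
- *The ICC of 0.05 is wrong.* The article openly labels it an assumption. The reported differences between centres concern family involvement practice, not variance in the outcome scores. With equal clusters and 12 df, power is 85% at ICC 0.02 and 59% at 0.10, so the sensitivity runs both ways. A range would inform readers, but its absence is not an error.
- *The trial's main question is underpowered.* The primary outcomes are the fidelity changes, which are sized separately.

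**Conclusion.** The point holds in limited form. With 7 clusters and 112 analysed per arm, the protocol's own effect, ICC and significance level give about 74% power for an unadjusted comparison on about 12 df, not 80%. If recruitment follows caseload, the figure is about 70%, conditional on that assumption. The shortfall of roughly 6 to 10 percentage points is the same as moving the difference detectable with 80% power from 0.50 to about 0.54-0.56 SD.

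Severity is moderate. The outcomes are secondary, the 0.5 SD was itself a convention, and baseline adjustment may recover the loss. The statement still deserves correction, because it is the stated reason for 7 clusters per arm and readers will use it to interpret a null result.

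**What to change.** Keep the recruitment target of 161 per arm and restate the power in the Sample size section, for example:

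*With 7 clusters and 112 analysed per arm, an ICC of 0.05 and a two-sided 5% test on about 12 degrees of freedom, an unadjusted comparison has about 74% power for 0.5 SD if cluster sizes are equal, and about 70% if recruitment is proportional to unit size. The difference detectable with 80% power is about 0.54-0.56 SD. Adjustment for the baseline score may recover some of this.*

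A short table of power over ICC 0.02 to 0.10 is optional. The cost is text only: design, recruitment and analysis do not change, and the stated power becomes less favourable.
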